### 2.3. Inclusion and Exclusion Criteria

The criteria for inclusion are established as follows: (i) a diagnosis of urinary incontinence or an overactive bladder, (ii) women aged over 45 years, (iii) a condition persisting for at least three months, (iv) meeting the criteria for selection as a candidate for neuromodulation treatment (urge urinary incontinence), and (v) fluency in either Spanish or English. Participants will be excluded if they fulfill any of the following criteria: (i) any past or planned surgeries in the lumbar or abdominal regions, (ii) the presence of fractures or serious medical conditions, (iii) being pregnant or having the potential to become pregnant during the study period, (iv) any neurological or psychiatric disorders, (v) having stress urinary incontinence, (vi) women with autoimmune diseases or cancer, (vii) fear of needles, and (viii) individuals who have previously undergone neuromodulation treatment.

### 2.4. Procedure

Once the groups have been assigned, four sample collections will take place at the following time points: Pre (baseline), Post_1month_, Post_3months_, Post_6months_ (Figure 2). All the participants will engage in 24 experimental sessions, each with a duration of approximately 60 min. At each assessment point, the studied variables will be monitored and recorded in the “Data Collection Notebook”. It has been created to systematically record both the primary and secondary outcome variables at each measurement point, in alignment with the study protocol.

## 3. Randomization and Blinding

The principal investigator, supported by a team of experienced physiotherapists with over a decade of expertise in neuromodulation and exercise therapy for UI, will oversee the implementation of the treatment protocol. Stratified randomization will be employed to ensure that the groups being compared are balanced in terms the specific levels of OAB-q SF [25]. The baseline OAB-q SF levels will be assessed before randomization, and the participants will be divided into two strata according to these levels, as outlined in the corresponding sections. One of the researchers will administer the interventions across all three groups, while the other will conduct the outcome assessments to maintain evaluator blinding. A block randomization design (block sizes of 4, 6, or 8) will be applied to ensure an equal number of participants in each group. To minimize the bias, the group allocation will be determined using a randomization table generated by an independent researcher using Excel. A double-blind design will be implemented to ensure objectivity.

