## Abstract

**Introduction:** Overactive bladder (OAB) and urinary incontinence (UI) are prevalent, particularly in older adults, and affect quality of life. OAB involves urgency, frequency, nocturia, and urgency incontinence, often linked to involuntary detrusor contractions. Treatment guidelines recommend a stepwise approach, starting with pelvic floor muscle training (PFMT), followed by pharmacological or minimally invasive therapies, such as neuromodulation. However, the combined effects of PFMT and neuromodulation have not been well established. This study aimed to evaluate the impact of combining pelvic floor exercises with neuromodulation versus PFMT with sham neuromodulation or standard physiotherapy after a 12-week intervention in individuals with OAB and UI. **Methods/Materials:** A double-blind, randomized controlled trial was designed with three groups: PFMT + neuromodulation, PFMT + sham, and conventional physiotherapy (control) in a 1:1:1 ratio. This study followed the CONSORT guidelines and was registered at ClinicalTrials.gov (NCT06783374). The sample size was calculated using GPower^®^ software, assuming a Cohen’s effect size of 1.04, a power of 0.80, an alpha of 0.05, and a 15% dropout rate, totaling 63 participants (21 per group). Participants attended 24 sessions over 12 weeks (2 sessions per week). The interventions were based on previously validated protocols. **Outcomes:** The primary outcomes included health-related quality of life, pelvic floor muscle function, pain, adherence, and general health. The secondary outcomes included Incontinence Quality of Life questionnaire, 3-day bladder diary, International Consultation on Incontinence Questionnaire–Urinary Incontinence Short Form, kinesiophobia, and electromyographic data.

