
## 2. Materials and Methods

### 2.1. Study Design

This study adopts a prospective, double-blind, randomized controlled trial (RCT) design with a comparative longitudinal approach. The study protocol has been developed following the SPIRIT guidelines, which delineate the essential components that must be incorporated into randomized clinical trial protocols (Figure 1) [22]. The results will be communicated in accordance with the Template for Intervention Description and Replication (TIDieR) checklist to provide a detailed and accurate description of the intervention and its implementation [23].

This double-blind study will include three groups: (i) an exercise program combined with neuromodulation, (ii) an exercise program with a sham neuromodulation procedure, and (iii) a control group receiving conventional physiotherapy treatment, with participants equally distributed among the groups. The Ethics Committee of the Catholic University of Valencia approved the study protocol (13 January 2025) (ID: UCV/-2025/020), and the trial was registered in the ClinicalTrials.gov database under registration number NCT06783374 (20 January 2025). The timetable for completion of the study is as follows: the study will begin on 4 March 2025, with primary completion expected by 10 November 2026. The intervention will be conducted at the Clinics of the Catholic University of Valencia. Prior to the intervention, participants will receive a detailed video briefing that will explain the study’s objectives, procedures, and possible risks. All the participants who agree to participate will provide written informed consent forms prepared in accordance with the ethical principles outlined in the Declaration of Helsinki [24].

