## 4. Sample Size

Statistical analysis was performed using a repeated measures analysis of variance (ANOVA), focusing on the primary variable, OAB-q SF. Drawing on a previous study on transcutaneous tibial nerve stimulation in women with idiopathic overactive bladder [26], the Cohen’s effect size was estimated to be 1.04. The statistical power was set at 0.80, with an alpha level of 0.05, considering the three intervention groups. Initially, 54 individuals were allocated to three groups (18 participants per group). To account for a potential 15% dropout rate during follow-up, three additional participants were added to each group, resulting in 21 participants per group and a total sample size of 63. The required sample size was calculated using G*Power software (version 3.1.9.2; Franz Faul, Universität Kiel, Kiel, Germany).

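### Block sizes 4 and 8 do not divide by three arms (6 does), so the stated randomisation scheme cannot guarantee equal groups

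*Protocol article*

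**What the plan says.** Section 3 (Randomization and Blinding) of the protocol article gives both the method and its purpose: "A block randomization design (block sizes of 4, 6, or 8) will be applied to ensure an equal number of participants in each group". The same section stratifies by baseline OAB-q SF: "the participants will be divided into two strata according to these levels". The list is to be produced in Excel by an independent researcher.

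Three other places fix what the list has to deliver. The Abstract gives three arms, the third being "conventional physiotherapy (control) in a 1:1:1 ratio". Section 2.1 repeats the intention, "with participants equally distributed among the groups". Section 4 sets the numbers, "resulting in 21 participants per group and a total sample size of 63".

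No part of the article says how a block of 4 or 8 is to be shared among three arms.

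**The concern.** A permuted block holds each arm in a fixed proportion. With three arms at 1:1:1, that is possible only when the block size is a multiple of three. Two of the three stated sizes are not, yet the article gives blocking as its means of making the groups equal.

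Whoever builds the list must therefore either drop two of the stated sizes or invent a rule for the surplus places. In both cases, what is done will differ from what is written or go beyond it. At stake are how well the arm sizes are balanced, whether the allocation probabilities are really equal, and whether the randomisation can be reported and reproduced as described.

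**Working it through.** **Inputs from the article.** Three arms at 1:1:1 (Abstract, Section 2.1); block sizes 4, 6 or 8 and two strata (Section 3); 18 per group before dropout, 15% dropout, 21 per group and 63 in total (Section 4).

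**The plan's own figure.** 18 + 3 = 21 per group and 3 × 21 = 63. Multiplying by 1 + dropout gives 54 × 1.15 = 62.1, rounded up to 63. Dividing by 1 − dropout gives 54 / 0.85 = 63.5, rounded up to 64. The target of 63 in three equal groups is thus reproduced to within one participant.

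**Divisibility.** Surplus places = block size mod 3.
- 4 mod 3 = 1: at best 2:1:1.
- 6 mod 3 = 0: exactly 2:2:2.
- 8 mod 3 = 2: at best 3:3:2.

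Every completed block of 4 or 8 leaves a difference of at least one between arms, and these differences can accumulate over blocks. With multiples of three, only the last unfinished block in a stratum can cause a difference. That difference is at most 1, 2 or 3 for a block of 3, 6 or 9. Over two strata with blocks of 3, 6 and 9, the total gap is therefore at most 3 + 3 = 6. The stated sizes carry no such limit. They are also all even, so no set of complete blocks adds up to 63.

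**Size of the imbalance by simulation.** Assumptions, because the article does not settle them: strata split about 50:50, block sizes equally likely, surplus places given to randomly chosen arms, N = 63. The gap is the largest minus the smallest arm over the whole trial. There were 6,000 runs for the equal-arms and mean columns and 10,000 for the last column.

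| Block sizes | Arms exactly equal | Mean gap | Gap of 4 or more |
|---|---|---|---|
| 4, 6, 8 | 9% | 2.9 | 31% |
| 3, 6, 9 | 33% | 1.5 | about 2% |
| 3, 6 | 41% | 1.2 | 0.4% |
| 6 only | 32% | 1.4 | not tabulated (largest gap seen was 3) |

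The largest gap seen with 4, 6 and 8 was 9. Under random filling each arm has the same expected size, 63 / 3 = 21.

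**Worst case: surplus always to the same arms.** One block of each size (4 + 6 + 8 = 18 places) then gives 2 + 2 + 3 = 7, 1 + 2 + 3 = 6 and 1 + 2 + 2 = 5. Scaled to 63, this is 63 × 7/18 = 24.5, 63 × 6/18 = 21 and 63 × 5/18 = 17.5. Simulation, which includes unfinished blocks, gives 24.6, 20.9 and 17.5, with a mean gap of 7.1.

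**Effect on power.** For one pairwise comparison by two-sided t-test at alpha 0.05, taking the stated effect size of 1.04 as a standardised difference between two arms and ignoring dropout:
- 21 v 21: 0.908
- 18 v 24: 0.902
- 25 v 17: 0.898

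**The case against.** The strongest reply is that little follows from the error. Unequal arm sizes do not in themselves bias a randomised comparison, and the mixed ANOVA in Section 8.2.2 does not need equal arms. The pairwise power above moves by 0.01 at most and stays above the 0.80 in Section 4. All of this stands, and it limits how serious the point is.

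Several stronger readings are tempting, but the article does not support them:

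- A reader might infer that none of the three sizes works. Size 6 does, and equal totals can still arise by chance with the others. What fails is the guarantee.
- A reader might infer that the benefit of blocking is lost. Under random filling most of it remains: the mean total gap is 2.9, against 7.8 with no blocking. Within a stratum it is 2.1, against 5.5 with no blocking and 1.0 with blocks of 3, 6 and 9.
- A reader might take 24.6/20.9/17.5 as the expected outcome. It needs a fixed-order rule that the article does not state. Rotating the surplus across arms within each stratum would give a mean gap of about 1.8, with 4 or more in about 6% of trials.
- A reader might infer that the stratification is unusable because no OAB-q SF cut-off is given. A journal article may leave that to the full protocol, so it forms no part of this point.

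It might also be said that the full protocol could rescue the scheme. It could supply a surplus rule, but it cannot make 4 or 8 divisible by three. Always pairing a 4 with an 8 would amount to a block of 12, which is not what is written.

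**Conclusion.** The error is real and can be seen from the article alone. Section 3 names block sizes of which two cannot produce the equal allocation that the same sentence promises and that the Abstract, Section 2.1 and Section 4 rely on.

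The divisibility result needs no assumption. The size of the effect does, because the surplus rule is unstated. With random filling, the cost is about 1.4 participants in the mean gap (2.9 − 1.5), and a gap of 4 or more is far more frequent than with 3, 6 and 9. Only a fixed-order rule would make the allocation systematically unequal.

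No bias and no material loss of power is shown. This is an error in the randomisation specification that should be corrected, and it does not undermine the trial.

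**What to change.** In Section 3, replace the three sizes with randomly varied multiples of three, and state that the sizes are concealed from the treating and the assessing researchers. Sizes 3, 6 and 9 would serve. Sizes 6 and 9 are preferable if predictability is a concern: in a block of 3 the last allocation follows from the first two, and one researcher delivers all three treatments and so sees the allocations. Size 6 alone also balances, but it makes the block size fixed.

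The article gives 4 March 2025 as the start date. If enrolment has begun, establish how blocks of 4 and 8 were filled, leave allocations already made as they are, regenerate only the unused part of the list, and report both what was done and when it changed.

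The cost is a line of protocol text and a new list for the remaining places. The sample size stays at 63, with no added participants or procedures. A small residual gap from unfinished blocks will remain under any blocked scheme, so the text should claim approximately equal groups.

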## 4. Sample Size

Statistical analysis was performed using a repeated measures analysis of variance (ANOVA), focusing on the primary variable, OAB-q SF. Drawing on a previous study on transcutaneous tibial nerve stimulation in women with idiopathic overactive bladder [26], the Cohen’s effect size was estimated to be 1.04. The statistical power was set at 0.80, with an alpha level of 0.05, considering the three intervention groups. Initially, 54 individuals were allocated to three groups (18 participants per group). To account for a potential 15% dropout rate during follow-up, three additional participants were added to each group, resulting in 21 participants per group and a total sample size of 63. The required sample size was calculated using G*Power software (version 3.1.9.2; Franz Faul, Universität Kiel, Kiel, Germany).

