#### 8.2.2. Analysis of the Outcome Measures

The assumption of normality will be evaluated using the Kolmogorov–Smirnov test, while the homogeneity of variances will be assessed with Levene’s test. A two-way mixed-design ANOVA will be employed, with the time serving as the within-subject factor and the treatment group as the between-subject factor. Tukey’s post hoc correction will be applied to examine the effects of both the primary and secondary outcomes. The results will be presented as the mean differences (MDs) with 95% confidence intervals (CIs). The effect sizes (ESs) will be calculated using Cohen’s d. In the event of participant dropouts during the study, or if the statistical power falls below the predetermined threshold of 80%, an intention-to-treat analysis will be conducted [62]. All the statistical analyses will be conducted by an independent researcher who will not be involved in the data collection and will utilize anonymized, coded datasets.

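### The evaluable sample of 54 does not follow from the inputs in Section 4, and the stated 80% power does not describe the Tukey-adjusted pairwise comparison that answers the objective

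*Protocol article*

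**What the plan says.** Section 4 (Sample Size) describes a "repeated measures analysis of variance (ANOVA), focusing on the primary variable, OAB-q SF". It takes a Cohen's effect size from an earlier study of transcutaneous tibial nerve stimulation and states: "effect size was estimated to be 1.04. The statistical power was set at 0.80, with an alpha level of 0.05". The calculation is for three groups, and G*Power is named as the software. The result is 54 participants, 18 per arm. On attrition it says: "To account for a potential 15% dropout rate during follow-up, three additional participants were added to each group, resulting in 21 participants per group", for a total of 63.

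Section 4 does not say whether 1.04 is d or f, which contrast it describes, which ANOVA effect was tested, how many measurements entered, or what correlation was assumed.

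Section 2.4 sets four measurement points. Section 8.2.2 plans a two-way mixed ANOVA (time by group) and then says: "Tukey’s post hoc correction will be applied to examine the effects of both the primary and secondary outcomes". It reports mean differences and expresses effect sizes as Cohen's d. The objective at the end of Section 1 compares exercise plus neuromodulation with exercise plus sham, or with conventional therapy.

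**The concern.** G*Power's ANOVA procedures take f as the effect size. The value 1.04 looks like a two-group d, and Section 8.2.2 uses d. Going from d to f with three groups requires an assumption about where the third mean lies. A repeated-measures procedure also requires a tested effect, a number of measurements and a correlation. Without these, a reader cannot tell what the 80% refers to.

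The objective will be answered by pairwise differences under Tukey's correction, and Section 4 gives no power for them. A reader will naturally take the 80% to cover neuromodulation versus sham. Both of those arms receive the exercise programme, so the contrast is only the increment from stimulation. A null result there could be presented as coming from an adequately powered comparison when that power was never calculated.

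**Working it through.** **Inputs.** From Section 4: effect size 1.04, power 0.80, alpha 0.05, three groups, 18 evaluable per arm, 21 enrolled per arm, 15% loss. From Section 2.4: four measurements. From Section 8.2.2: time-by-group mixed ANOVA and Tukey. Assumed here: two-sided pairwise tests, equal arms and, for repeated measures, sphericity.

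**1. Trying to reproduce 54.**

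One-way ANOVA has noncentrality λ = N·f² with 2 and N − 3 degrees of freedom. The smallest equal-arm N with at least 80% power is:

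| Reading of 1.04 | f | N needed |
|---|---|---|
| d, third mean midway: d/√6 | 0.425 | 57 |
| d, one arm apart from two equal arms: d·√2/3 | 0.490 | 45 |
| d, two-group rule: d/2 | 0.52 | 39 |
| already f | 1.04 | 15 |

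For the first row, f² = 1.0816/6 = 0.1803. At N = 54, λ = 9.73 and power is 77.9%.

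For the time-by-group interaction, λ = N·f²·m/(1 − ρ), with 2(m − 1) and (N − 3)(m − 1) degrees of freedom. Across the four values of f, m = 2 to 4 measurements and ρ = 0 to 0.9, the required N runs from 6 to 30. The maximum of 30 occurs at f = 0.425, m = 2, ρ = 0.

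For the repeated-measures between-groups effect, λ = N·f²·m/(1 + (m − 1)ρ). With m = 4 and ρ = 0.5, N is 39, 30, 27 or 12 for the four values of f in the order of the table. At f = 0.425 the answer is 54 for m = 2 with ρ = 0.8 to 0.9, and for m = 3 or 4 with ρ = 0.9. For example, at m = 4 and ρ = 0.9 the factor is 4/3.7 = 1.081, λ = 10.52 and power at 54 is 81.2%.

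A plain two-sided t-test at d = 1.04 needs 16 per arm. Eighteen per arm can also be reached by a normal-approximation two-sample formula at alpha/2, or by a one-sided t-test at alpha/3. Section 4 states neither.

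**2. Power of one Tukey-adjusted pair, single time point, no baseline adjustment.**

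With n = 18 per arm, df = 3 × 17 = 51. The critical value is the 95% point of the studentised range for three groups divided by √2, which is 2.414. The noncentrality is d·√(n/2) = 1.04 × 3 = 3.12. Power is the probability that a noncentral t with 51 df exceeds 2.414 in absolute value.

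| d | Completers per arm | Power |
|---|---|---|
| 1.04 | 18 | 75.8% |
| 1.04 | 20 | 80.8% |
| 1.04 | 21 (no loss) | 83.0% |
| 0.8 | 18 | 50% |
| 0.7 | 18 | 38% |
| 0.5 | 18 | 19% |

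The smallest d detectable with 80% power at 18 per arm is 1.09.

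**3. The same pair with baseline adjustment.**

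Assume a baseline correlation of 0.5, which the document does not give. The residual SD shrinks by √(1 − 0.25) = √0.75, so the effective d is 1.04/0.866 = 1.20. The noncentrality is 3.60 and power is 87.9%. For d = 0.8 the effective value is 0.92 and power is 64%. For d = 0.5 it is 0.58 and power is 26%.

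**4. Dropout.**

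The stated 21 matches 18 × 1.15 = 20.7, rounded up. Dividing instead gives 18/0.85 = 21.2 per arm, or 54/0.85 = 63.5 in total. With 21 enrolled, 21 × 0.85 = 17.85 per arm and 63 × 0.85 = 53.55 in total. Three of 21 is 14.3%. At 17.85 per arm the Tukey power is 75.3%, against 75.8% at 18.

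**The case against.** The best defence is that Section 4 names a repeated measures ANOVA, not a one-way ANOVA, and a between-groups effect at f = 0.425 with high correlation does return exactly 54. At that f, 54 participants give 80% to 94% power for every m from 2 to 4 and ρ from 0.5 to 0.9 tried. Section 4 attaches its 80% to an ANOVA and never claims it for a Tukey pair. Pairwise power is 83.0% if nobody is lost, and about 88% with baseline adjustment at a correlation of 0.5.

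All of this stands, and it rules out three inferences a reader might draw.

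- That 54 is wrong for the named test. The stated inputs do not fix the number, but some settings of that test give it.
- That the trial has 76% power where it promised 80%. Those figures belong to different tests.
- That 1.04 is shown to be too large because the source used transcutaneous stimulation and both key arms exercise. The source study's contrast and arms cannot be seen from this document. This is a reason to show a range of d, not proof of an error.

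The dropout gap is also a rounding matter: under half a participant in total and about 0.4 percentage points of power.

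The defence does not rescue the section as written. Every route to 54 needs a choice that Section 4 omits, and plausible choices give anything from 6 to 57. The article chose to report the calculation, so its inputs should yield its answer.

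**Conclusion.** The point holds in this form: 54 does not follow from the inputs stated, and the only power figure given does not describe the Tukey-corrected comparison that answers the objective. For that comparison, power at d = 1.04 with 18 completers per arm is 75.8%, falling to 50% at d = 0.8 and 19% at d = 0.5. These figures assume a single time point, a two-sided test, equal arms, a common variance and no baseline adjustment. Adjustment at an assumed baseline correlation of 0.5 raises the first to about 88%. It does not restore 80% at d = 0.8 (64%) or d = 0.5 (26%). The calculations do not show that the trial is too small for its named ANOVA. The dropout wording is a minor correction.

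**What to change.** Restate Section 4 so that the number can be checked. Say whether 1.04 is d or f, how any conversion was made, which effect was tested, how many measurements entered and what correlation was assumed.

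Then report the power of neuromodulation versus sham under Tukey's correction over d = 0.5 to 1.04, with 18 completers per arm. Without baseline adjustment this is about 76% at d = 1.04, 50% at 0.8 and 19% at 0.5. If the analysis is baseline-adjusted, give about 88% at d = 1.04 and label the correlation of 0.5 as an assumption. Do not attach the 76% to a baseline-adjusted analysis.

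Restate the dropout allowance as about 14%.

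The cost is a rewritten paragraph with somewhat less favourable figures. No extra enrolment and no change to treatment or assessments is needed.
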